#### 2.2.7 Physical Fitness

Physical activity is defined as any bodily movement produced by skeletal muscles that results in energy expenditure. Physical fitness, on the other hand, characterizes the physiologic state of an individual, including aerobic power, muscular endurance, muscular strength, body composition, and/or flexibility. Both physical activity and fitness are independently related to changes in insulin sensitivity and improvement in the pathophysiology of T2DM. Those who are more active and expend more energy have higher fitness levels. However, there is only a moderate relationship between physical

activity and physical fitness [Jacobs 1993]. Therefore, the effect of the treatment interventions on both of these measures is compared.

Cardiorespiratory fitness is defined as the ability to absorb, transport, and use oxygen. Higher maximal oxygen uptake ( $\text{VO}_2$  max) values indicate better cardiorespiratory fitness. Ideally it is assessed by direct measurement of oxygen uptake during a graded exercise test (GXT) on a treadmill or cycle ergometer. The measurement of  $\text{VO}_2$  max is a challenging task in children [Rowland and Cunningham 1992; Howley 1995]. Motivating youth to exercise maximally is difficult and they may have difficulty obtaining  $\text{VO}_2$  max. Furthermore, these tests require expensive metabolic measuring systems and take approximately an hour to complete.

Because of these difficulties, investigators have resorted to predicting  $\text{VO}_2$  max. The most popular methodologies to predict  $\text{VO}_2$  max in children have utilized cycle ergometry to determine the physical work capacity or PWC [Boreham 1990]. These tests involve obtaining heart rates at three submaximal workloads, plotting these heart rates against the workload, extrapolating to determine the workload at a given heart rate or at maximal heart rate, and then converting that maximal workload to oxygen uptake. Participants sit quietly while their heart rate is measured, until they have adapted to the laboratory and their heart rate is stable. They then begin the multistage fitness test, beginning at 150 kpm and increasing in 150 kpm increments every three minutes until a heart rate of 160 bpm is reached. The work required to produce a heart rate of 160 bpm is used to extrapolate the PWC at a heart rate of 170 bpm. This prediction of  $\text{VO}_2$  max has several advantages. First, the PWC equipment and space needs are modest. Second, the PWC can be administered in 12-15 minutes and requires only the measurement of heart rate. Third, the PWC is ideal to use in a test-retest protocol since learning, practice, or training have little effect on its results.

In this protocol, participants undergo PWC 170 testing at baseline, six months, two years, primary endpoint, and end of study, and the effects of the three treatment arms on fitness are compared.

### 2.2.8 Cardiovascular Risk Factors

Both obesity and T2DM are associated with a significantly increased risk of cardiovascular morbidity and mortality in adults, and insulin resistance, present in both conditions, has been considered the underlying pathologic mechanism. Previous studies on adult populations have consistently demonstrated the associations among insulin resistance, hyperinsulinemia, and the traditional cardiovascular risk factors of hypertension and dyslipidemia [Reaven 1988; Zavaroni et al. 1989; Zavaroni et al. 1990]. However, the association with these traditional risk factors accounts for only approximately 50% of the cardiovascular risk associated with hyperinsulinemia and insulin resistance, an observation that has led to the identification of a number of 'non-traditional' risk factors for cardiovascular morbidity [Kullo et al. 2000]. In general, these newly identified risk factors indicate alterations in hemostasis and the presence of acute and chronic systemic inflammation. For example, increased risk of cardiovascular disease has been associated with alterations in the fibrinolytic pathway and other aspects of hemostasis, including regulation of the equilibrium between tissue-type plasminogen activator (t-PA) and its inhibitor plasminogen activator inhibitor-1 (PAI-1), von Willebrand factor, and factor VII antigen [De Maat et al. 1996; Juhan-Vague et al. 1999; Meigs et al. 2000]. Similarly, increased cardiovascular risk has been associated with a wide variety of markers that indicate a state of chronic inflammation, including white blood cell count, C-reactive protein, IL-6, TNF- $\alpha$ , and other acute phase reactants [Kullo et al. 2000]. The recognition of the relationships among these factors has drastically altered our understanding of the pathophysiology of insulin resistant

version 1.9, January 24, 2011

states and lead to reconsideration of the mechanism of action of a variety of agents, including the insulin-sensitizing thiazolidinediones.

Among children, less is known about the relationship between obesity, insulin resistance, T2DM, and cardiovascular risk. Several large epidemiologic studies in youth have shown an association between obesity, traditional risk factors (e.g., hypertension and dyslipidemia), and cardiovascular disease [Srinivasan et al. 2002; Zieske et al. 2002]. However, little is known about the non-traditional risk factors. In small series, obese children and adolescents have been found to have increased levels of fibrinogen, PAI-1, and D-dimer, as well as abnormalities in factor VIIc, von Willebrand factor, PAI-1, fibrinogen, and tissue plasminogen activator [Ferguson et al. 1998; Gallistl et al. 2000; Sudi et al. 2001]. Following weight loss interventions, decreased levels of PAI-1 and IL-6 have been demonstrated [Estelles et al. 2001; Gallistl et al. 2001] suggesting that lifestyle interventions may be able to alter cardiovascular risk in young patients.

These studies suggest that among obese adolescent patients with T2DM, there may be unfavorable patterns of both traditional and non-traditional risk factors implicated in cardiovascular morbidity and mortality. The development of cardiovascular risk is an important consideration in comparing the efficacy and long-term implications for the treatment interventions under study in this trial. To address this, the differential effects of the three treatment arms on both traditional and non-traditional markers are compared. Blood pressure is measured at every visit and specimens drawn for repeated measurements of lipids (free fatty acids, lipoprotein subclass levels, average LDL particle density, and total ApoB level), fibrinogen, c-reactive protein, plasminogen activator inhibitor-1, homocysteine (vitamin B-12 will be determined to evaluate homocysteine levels), and interleukin-6 at baseline, six months, annually, primary endpoint, and end of study.

#### 2.2.9 Microvascular Complications

Microvascular complications associated with diabetes produce significant burdens for the individual patient and are responsible for a major part of the public health care costs associated with diabetes. Microvascular complications are more common among children with T2DM at the time of presentation than among those with type 1 diabetes (T1DM) [Takahashi et al. 1990; Yokoyama et al. 2000]. There is evidence, although limited, that suggests that progression rates of microvascular complications are also greater in youth with T2DM. Therefore, a comparison of the effect of the treatment interventions on the prevention and slowing of rates of development of microvascular complications associated with T2DM is an important secondary outcome of TODAY and could significantly modify the interpretation of the primary outcome results.

Quantitation of microalbuminuria is performed by obtaining spot urine measurements of microalbumin/creatinine ratio at baseline and annual visits. Abnormal values on spot urines are confirmed with two additional spot urine samples within three months; diagnosis of microalbuminuria is made as a result of two out of three positive tests. Creatinine clearance (by calculation) is determined at baseline and annual visits. Abnormal values are monitored more frequently. Results are compared for the three treatment regimens.

The presence of peripheral neuropathy is evaluated using the Michigan Neuropathy Screening Instrument (MNSI) [Feldman 1994], a simple and well-validated screening tool for detection of peripheral neuropathy in patients with T2DM. MNSI screening is performed at baseline, annual visits, primary endpoint, and end of study.

Retinopathy also appears to have increased in prevalence among children with T2DM at presentation [Yoshida et al. 2001], though data are limited to small case series. Due to financial limitations, routine identification and monitoring for retinopathy was not undertaken as a primary component of TODAY, though participants were encouraged to undergo

screening according to ADA Clinical Practice Guidelines and results of screening were obtained. However, in the final year of the study, all TODAY participants undergo retinopathy screening, including dilated retinal exam and retinal photography. Results are compared for the three treatment regimens.

#### 2.2.10 Cardiac Function

Type 2 diabetes is associated with functional and anatomic changes in the heart in adults, including left ventricular and septal hypertrophy, decreased ejection fraction, and decreased distensibility. However, little is known about the association of type 2 diabetes and alterations in cardiac function in adolescents. Two recent papers [Chinali et al. 2008, Nadeau et al. 2009] report left ventricular hypertrophy and decreased cardiac adaptation to exercise in small groups of adolescents with type 2 diabetes compared to their obese non-diabetic peers. In the last year of TODAY, cardiac function is evaluated in all participants by resting echocardiography. Results are compared for the three treatment regimens.

#### 2.2.11 Quality of Life and Psychological Measures

The psychological, emotional, and social status of a patient interacts with his or her chronic illness in complex ways. Difficulties in the family social or psychological structure can hasten onset of lifestyle related disorders, such as T2DM, and then further interfere with treatment. Onset of a chronic illness, particularly one that requires significant personal change, can adversely affect many aspects of a patient's and family's emotional well being. This intervention trial examines whether psychological characteristics of patients influence treatment outcome and whether the interventions have an effect on psychological problems and quality of life. The following questions are of interest: (1) whether the participant's and/or parents' psychological status at baseline has an important effect on the success of the three treatment arms, (2) whether the treatment assignment has an effect on psychological outcomes related to the diagnosis of diabetes, and (3) whether changes in the family support person's psychological status affect outcomes.

In the child, responses to psychological problems and quality of life measures are compared among the treatment groups at baseline, six months, 2 years, primary endpoint, and end of study using standardized and validated instruments. The specific instruments to assess psychological problems include: the Children's Depression Inventory (CDI) (up to age 16) [Kovacs 1981; Kovacs 1985; Kovacs 1992; Kovacs and Beck 1997; Reynolds 1992], the Beck Depression Inventory (BDI) (beginning at age 16) [Beck et al. 1961; Beck et al. 1988; Beck and Steer 1993; Beck and Steer 1996; Kendall et al. 1987], the Eating Disorders Examination Questionnaire (EDEQ), the Questionnaire on Eating and Weight Pattern–Revised (QEWP-R) (only if indicated by the score on the EDEQ) [Landgraf et al. 1996]. Quality of life is assessed using the Pediatric Quality of Life [Varni et al. 2003] for evaluation of health related quality of life.

The biological parent also completes the BDI, EDEQ, and QEWP-R (only if indicated by the score on the EDEQ) at baseline. The FSP completes the BDI, EDEQ, QEWP-R (only if indicated by the score on the EDEQ), Pediatric Quality of Life (adult proxy) and CHQ (P28) at baseline and 24 months.

At the end of study, a psychosocial inventory is completed by study staff in order to assist participants in their transition out of the TODAY study into regular clinical care and to provide appropriate direction to community resources. These data will also be used to describe the psychosocial challenges experienced by TODAY study participants.

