
A number of indices based on fasting measurement of glucose and glucose regulating hormones such as insulin (including C-peptide) and proinsulin have also been proven to closely correlate with corresponding clamp-derived indices of insulin sensitivity and secretion in diverse pediatric populations [Bonora et al. 2000; Hermans et al. 1999; Katz 2000; Guzzaloni 2002; Uwaifo 2002]. Since it is easy to obtain fasting blood tests, evaluation of these measurements to assess insulin sensitivity and secretion is ideal for a large clinical trial. HOMA-R (resistance) and B (secretion) are calculated using a computer-based model solution. QUICKI is calculated as  $1/(\log[I_0] + \log[G_0])$ .

Insulin sensitivity and secretion are determined with fasting glucose, insulin, C-peptide, and proinsulin levels, OGTT, HOMA, and QUICKI at baseline, 6 months, annually, primary endpoint, and end of study and are compared among the three treatment arms.

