Height and weight are measured at each study visit. Participants undergo other anthropometric measurements and DXA analysis of body composition at baseline, six months, two years, primary endpoint, and end of study; results are compared among the three treatment arms.

In addition, biological parent height and weight are collected at baseline in order to evaluate the predictive effect of parent BMI on outcomes. Height and weight are collected from the family support person (FSP) on an annual basis in order to determine the effect of FSP weight loss or participation in the lifestyle intervention with participant anthropometrics and body composition.

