#### 4.2.1.2 Rosiglitazone

Patients who are randomized to metformin plus rosiglitazone treatment group are started on a dose of 2 mg rosiglitazone bid. After 8 weeks, the dose is increased to 4 mg bid. Patients who reach the primary endpoint and begin add-on insulin therapy (see section 4.7) have the rosiglitazone dose lowered to 2 mg bid.

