## 5 Research Procedures and Approach

### 5.1 Data Collection

The table lists the schedule of data collection, measurements, and assessments.

| Data Collection                      |                                           |                                              |                 |                                          |                                                                                                                            |
|---------------------------------------------|-------------------------------------------|----------------------------------------------|-----------------|------------------------------------------|----------------------------------------------------------------------------------------------------------------------------|
| Measurement/
Assessment          | Eligibility
Initial
Screen | Run-in
L=last
run-in
only | Baseline | Year 1
X = every 2
months | Post Year 1 Follow-up
Q = quarterly; A = annual
24 = 24 months
P = primary outcome
E = end of study |
| Historical data (a)                         | X                                         |                                              | X               |                                          |                                                                                                                            |
| HbA1c                                       | X                                         | X                                            | (p)             | X                                        | Q, A, 24, P, E                                                                                                             |
| Blood for storage                           |                                           |                                              | X               | 6,12                                     | A, 24, P, E                                                                                                                |
| Blood for DNA                               |                                           |                                              |                 | (q)                                      | (q)                                                                                                                        |

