## 8.2 Statistical Analysis

The principal analyses of primary and secondary outcomes employ the "intent-to-treat" approach [Peduzzi et al. 1993]. The intent-to-treat analyses include all randomized patients with all patients included in their randomly assigned treatment group; treatment group assignment is not altered based on the patient's adherence to the assigned treatment regimen. All statistical tests are two-sided with the overall significance level of the primary outcome  $\alpha$

$\alpha = 0.05$ . However, b

TODAY, the significance levels used in the interim and final analyses of the primary outcome are adjusted to account for the multiplicity of interim analyses.

- *Baseline characteristics:* Comparison of the baseline characteristics among the three treatment groups uses standard nonparametric statistical techniques, such as Fisher's exact test for categorical data and the Kruskal-Wallis test for ordinal or continuous data.
- *Primary outcome:* The principal analysis of TODAY is an analysis of the time to treatment failure. Turnbull's [1976] algorithm is used to calculate and compare Peto's [1973] nonparametric estimates of the interval-censored survival curves for each treatment group. For the primary outcome analysis, patients are considered "administratively censored" if they complete the full duration of TODAY without having failed. Patients who prematurely discontinue their follow-up visits without having reached study endpoint are "censored" as of their last follow-up visit. Failure is considered to have occurred during the interval between the last HbA1c value  $< 8\%$  and the first HbA1c value used to classify the participant as a treatment failure.
- *Secondary outcomes:* Secondary time to "event" outcomes (e.g., cardiovascular risk factors, microvascular outcomes) are analyzed using the same life-table methods described above for the primary outcome. A proportional-hazards regression model is used to evaluate potential covariates that may modify the primary and secondary time to

event outcomes (e.g., risk population defined by race/ethnicity, age, clinical site). Graphical procedures are used to assess the proportionality assumption. If the proportionality assumption is found to be unreasonable, then other models such as the accelerated failure time model [Wei 1992] or the proportional odds model [McCullagh 1980] are used to evaluate the covariates.

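### Section 2.2.11 compares arms on psychological and quality-of-life measures at the primary endpoint visit, which only patients who fail treatment have, so that contrast is not randomized

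*Protocol*

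**What the plan says.** Section 2.2.11 attaches the list of time points directly to the comparison: psychological problems and quality of life in the child "are compared among the treatment groups at baseline, six months, 2 years, primary endpoint, and end of study".

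Three other sections name the same visit in a measurement schedule and then say that arms are compared:

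- 2.2.3 (insulin sensitivity and secretion): "primary endpoint, and end of study and are compared among the three treatment arms".
- 2.2.4 (anthropometrics and DXA): "primary endpoint, and end of study; results are compared among the three treatment arms".
- 2.2.7 (PWC 170): "primary endpoint, and end of study, and the effects of the three treatment arms on fitness are compared".

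The schedule in section 5.1 defines the visit by the event: "P = primary outcome". Sections 2.1 and 8.1 define that outcome as treatment failure. Section 4.2.1.2 speaks of "Patients who reach the primary endpoint and begin add-on insulin therapy". Section 4.7 places a full outcomes assessment before add-on insulin starts and waives it if one was completed in the previous three months.

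Section 8.2 applies intent-to-treat to the principal analyses of both primary and secondary outcomes: "The intent-to-treat analyses include all randomized patients with all patients included in their randomly assigned treatment group". It assigns repeated measures, with quality of life among the examples, to longitudinal methods. It does not say how an event-triggered visit enters those methods, or that results at that visit are descriptive.

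**The concern.** A patient who never fails has no primary endpoint visit. Membership of a comparison at that visit is therefore decided after randomization, by the outcome that the regimens are meant to change. If one regimen prevents failures, the patients who still fail on it are on average a higher-risk group than those who fail on the other regimen. The arms can then differ at this visit on a measure that treatment does not touch, and the difference runs against the more effective arm.

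Section 2.2 says that the secondary outcomes help to interpret the primary result and give insight into mechanism. A contrast among failures alone, read as a treatment effect, could mislead that reading.

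**Working it through.** **Inputs from the Protocol.** Sections 2.1 and 8.1: 250 per arm; failure per six months of 10% v 5% or 20% v 12%, beginning at the first annual visit; 10% dropout per six months; two-sided 0.05 with Bonferroni for three comparisons. Section 1.2: three years of recruitment and at least two years of follow-up. Section 3.1 gives four years of recruitment, so both were run.

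**Assumptions.** Failure and dropout are exponential and recruitment is uniform. The failure hazard starts at month 6, so that the first failures are counted at the 12-month visit.

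**1. The plan's own figure.** Hazards per year are -2 ln(1-p): 0.211 v 0.103 and 0.446 v 0.256. Over three years of recruitment the model gives 122 and 218 events in two arms of 250. Power is Phi(|ln HR| x sqrt(d)/2 - 2.394), where 2.394 is the normal quantile for 0.05/3 two-sided.

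- HR 0.50, d = 122: 0.693 x 11.05/2 - 2.394 = 1.43, power about 92.5%.
- HR 0.60, d = 218: 0.511 x 14.76/2 - 2.394 = 1.38, power about 91.6%.

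The stated power of at least 90% is reproduced, which supports the month-6 reading. With onset at month 12 and three years of recruitment, power is 85-91%.

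**2. Who would have the visit.** The share failing while under observation is the integral of lambda x exp(-delta t - lambda(t-0.5)) x G(t) from t = 0.5 years. Here delta = -2 ln 0.9 = 0.211 per year, and G(t) is the probability that administrative follow-up reaches t.

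| Failure per 6 months | Three-year recruitment | Four-year recruitment |
|---|---|---|
| 10% v 5% | 31% v 18% | 34% v 19% |
| 20% v 12% | 51% v 36% | 53% v 38% |

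**3. When it falls.** With three-year recruitment and month-6 onset, mean time to failure among failures is 1.71 v 1.81 years (10% v 5%) and 1.53 v 1.67 years (20% v 12%). Over all variants of onset and recruitment the gap is 0.08-0.22 years, about 1 to 2.6 months.

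**4. Size of the selection effect.** This needs a figure that the Protocol does not give. Let U be a standard normal measure that treatment does not affect, and multiply the failure hazard by exp(bU), with b assumed between 0.3 and 1.0. Using step 2's hazards and dropout, month-6 onset, three-year recruitment and 2,000,000 simulated patients per arm:

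| Scenario | b | Share with the visit | Spurious difference (SD) | Standard error at 250 per arm |
|---|---|---|---|---|
| 10% v 5% | 0.3 | 32% v 18% | 0.04 | 0.19 |
| 10% v 5% | 1.0 | 35% v 22% | 0.13 | 0.16 |
| 20% v 12% | 0.3 | 51% v 36% | 0.05 | 0.14 |
| 20% v 12% | 1.0 | 50% v 39% | 0.11 | 0.12 |

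The standard error is sqrt(s1^2/n1 + s2^2/n2) among failures. For 10% v 5% at b = 1.0: n1 = 250 x 0.348 = 87, n2 = 250 x 0.220 = 55, and sqrt(0.90^2/87 + 0.91^2/55) = 0.156.

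A weaker link was also run: log-normal frailty with SD 0.5-1.0, correlated 0.3-0.7 with the measure, onset at month 12. It gave 0.02-0.08 SD and a rejection rate of 5.1-7.5% at a nominal 5%. The difference over all randomized patients was about zero.

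**The case against.** Three points on the other side carry weight.

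- **Measuring is not comparing.** In 2.2.3, 2.2.4 and 2.2.7 the list of times governs when measurements are taken, and a separate clause says that results or effects are compared. A reader might infer that all four sections plan a stand-alone contrast at failure; only 2.2.11 says so. This stands. What remains against the other three is that they do not set the visit apart.
- **Section 8.2 already names longitudinal methods.** It does, and the details of how visits enter a model may properly sit in an analysis plan that is not shown. That disposes of any complaint about missing model detail. It does not dispose of the sentence in 2.2.11, which states a comparison.
- **Intent-to-treat is not flatly contradicted.** Section 8.2 speaks of principal analyses and of keeping patients in their assigned group. Nothing calls a contrast at failure principal, and comparing by assigned arm moves nobody. A reader might infer an outright contradiction; the text supports one only if that contrast is treated as a principal analysis.

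Two further inferences go too far. The Protocol does not say that the visit falls at different times by arm; that follows only if failure rates differ, and the gap in means is then shorter than one quarterly visit interval. And a calculation that ignores dropout and the delayed onset of failure would put the shares at about 52% v 31-35% in the 10% v 5% scenario, which is too high under section 8.1's own assumptions.

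**Conclusion.** The point holds in a limited form. Section 2.2.11 states a between-arm comparison at a visit that exists only after treatment failure, and three other sections leave room for one. Such a contrast conditions on the primary outcome and would leave out about half to four-fifths of each arm, unequally between arms.

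The shares rest on the Protocol's rates and the month-6 reading of when failures begin. The bias rests on an assumed link between measure and failure. Across the range examined it is small and below one standard error, so the case for change is that the quantity being compared is badly defined; a large distortion has not been shown. Baseline, six-month, two-year and end-of-study comparisons do not depend on failure. The primary analysis and the sample size are untouched.

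**What to change.** In 2.2.11, take the primary endpoint out of the times at which arms are compared, and state separately that it remains an assessment visit.

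In 2.2.3, 2.2.4 and 2.2.7, leave the measurement schedule unchanged; deleting the visit there would remove assessments that section 5.1 requires. Add one sentence to each (or one for all in 2.2): arms are compared by time since randomization in all randomized patients, using the longitudinal methods of 8.2, with primary endpoint values entered at their actual time; results at failure by arm are descriptive only.

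The cost is wording in four sections. No visit, measurement, sample size or clinical rule changes.
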